### Experimental design

This study protocol is based on the SPIRIT 2013 clinical trial protocol guidelines [52,53] (S1-S3 File) and follows a randomized, controlled, partially-blind design. This study will be conducted during a specially designed summer golf training camp, with all experimental procedures carried out within the camp period. During this time, all participants will follow the same diet, daily schedule, training, and competition routines to minimize dropout and external interference. The study consists of three main phases (Fig 2): familiarization with the experimental procedure, baseline testing, and the formal experiment. During the formal experiment, participants will be randomly assigned to one of the following three groups: (MF-Mu Group) Participants undergo a mental fatigue induction task followed by a music intervention; (MF-nMu Group) Participants undergo a mental fatigue induction task but do not receive a music intervention; (CON Group) Participants neither undergo a mental fatigue induction task nor receive a music intervention.

**Fig 2 pone.0337905.g002:**
[figure not shown]
Overview of the experimental design.

Randomization of group allocation and participant order will be conducted using a random number table generator (www.randomizer.org), ensuring that no one can predict the group assignments before randomization. Participants will not be informed of the true purpose of the study; instead, they will be told that the study is part of a summer golf training camp and that they should perform their best during the skill testing phase. During the intervention, dedicated assistants will be responsible for inducing mental fatigue and administering the music intervention, but they will not be informed of the specific research objectives. During the golf skill testing and performance recording phase, testing assistants will be responsible only for recording test results and will not be aware of the participants’ group assignments. Data analysis will be conducted by researchers who only have access to anonymized data. Group assignment information will only be disclosed to the on-site medical team in case of participant health concerns. This design is conducive to blinding control. [54–56].

The total intervention duration is 45 minutes, consisting of 30 minutes of mental fatigue induction and 15 minutes of music intervention. Participants not undergoing mental fatigue induction will read some magazine leisurely, a common control in mental fatigue trials [57–59]. Those not receiving the music intervention will sit quietly and rest, a common control in music intervention trials [60–62], to control external factors and maintain consistent conditions. Immediately after the intervention, participants will complete golf skill testing, with the testing site located within a 2-minute walking distance from the intervention area. Performance outcomes include driving performance, iron shot performance, chipping performance, and putting performance. Golf skill test data will be collected on-site by assistant researchers and verified and signed off by a national-level referee to ensure validity.

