### Participants

Following recommendations from Lakens [49] and Aberson [50], powering for interaction effects is considered essential in behavioral intervention trials where the primary interest lies in differential changes across conditions. Accordingly, the sample size calculation is based on the statistical power required to detect a time × group interaction effect, estimated using the “ANOVA: Repeated measures, within–between interaction” model in G*Power 3.1. Assuming a medium effect size f = 0.25 (Cohen’s standard), α = 0.05, power = 0.95, three groups, two measurement time points, and an intra-class correlation (ICC) of 0.5, the estimated result shows that the study requires at least 66 participants (22 per group) to ensure sufficient power for detecting the interaction effect. Considering a potential dropout rate of 15% [51], a total of 76 golfers will be recruited. If practical resource constraints result in a slightly smaller sample size, the study will report effect sizes and Bayes factors to supplement the interpretation of statistical significance and cautiously delimit the generalizability of conclusions to ensure the scientific rigor and interpretability of the results.

Participants in this study will be selected from the National Colleges and Universities Golf Championship (NCUGC) in China. The research team will collaborate with the head coaches of the participating teams to determine the universities willing to participate. Subsequently, the head coaches and team physicians will conduct an initial screening of players based on the inclusion criteria set for this study (Table 1). The research team will then verify the eligibility of the selected participants before the experiment begins.

**Table 1 pone.0337905.t001:** Participant selection criteria.

Inclusion criteria	Exclusion criteria
Aged 18–24 years old	Color blindness
Golfers of the NCUGC	Hearing loss
Least 3 years of specialized golf training	Insomnia
Least 5 trainings per week	Experiencing any physical injury
	Experiencing mental health issues
	Receiving any medication

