### Intervention protocols

The experiment will be conducted at the university’s golf training facility under the supervision of professional members of the research team, including the university team’s head coach, team doctor, and a national-level golf referee. Data will be collected before and after the intervention, covering questionnaire assessments and golf skill tests. The baseline test and the formal test will be one week apart, and the experiment will take place on the same day of the week and at the same time (9:00–11:00 AM) to ensure sufficient recovery time and minimize the interference of residual effects [55,63,64].

During the mental fatigue induction phase, a 30-minute Stroop task will artificially induce mental fatigue, simulating the mental fatigue state that athletes experience during competitions or training sessions [65]. The Stroop task is a classic cognitive control task widely used for inducing mental fatigue. Research in sports science has shown that a 30-minute Stroop task significantly increases subjective fatigue and reduces sports performance [21,24]. This study will use a smartphone-based version of the Stroop task, where colour words (such as “red” and “blue”) are displayed continuously, but the font colour does not match the word’s meaning. Participants must ignore the word’s meaning and respond only based on the font colour. The Stroop task requires sustained attention, conflict resolution, and cognitive inhibition, leading to cognitive resource depletion and mental fatigue accumulation. During the experiment, all participants will use their smartphones (with brightness and touch sensitivity standardised) and wear earphones to minimise external distractions. Participants in the MF-Mu and MF-nMu groups will undergo mental fatigue induction, while those in the CON group will only read a golf magazine in a relaxed manner.

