### Data management

All participants signed informed consent forms and voluntarily participated in the experiment. Data management in this study strictly adheres to the General Data Protection Regulation of April 27, 2016, ensuring data confidentiality. The collected data will be used solely for academic research and will not be utilized for any commercial purposes. Participation in this study implies that subjects agree to allow researchers to collect their data and publish the research results in scientific journals. Participants retain the right to access their collected data and may request corrections if errors are found. Additionally, they have the right to withdraw from the study at any time without providing any reason.

All data will be recorded and entered by members of the research team. Psychological measurement data and skill performance data will be documented using paper-based questionnaires and forms. To ensure participant privacy and data security, paper-based data will be entered into the researchers’ electronic database within 24 hours and immediately destroyed. All data will be anonymized using coded identifiers to protect participant identities, with data access restricted to research team members. During data collection, the research team will implement quality control measures, including data integrity checks, cross-checking, and error correction. All electronic data will be regularly backed up, with backup files stored in a cloud storage system. Research findings and data analysis will be made publicly available through peer-reviewed journals or conference presentations.

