### Statistical analysis

All statistical tests will be conducted at a significance level of α = 0.05, with effect sizes measured using partial eta squared (η²p). The statistical power is set at 0.80, and all analyses will be performed using IBM SPSS Statistics 27.0. This study will adopt a 2 (Time: pre-test vs. post-test) × 3 (Group: mental fatigue–music intervention group, mental fatigue–non-music group, control group) mixed-design repeated measures ANOVA to examine the effects of mental fatigue and music intervention on golf-specific skill performance. The core hypothesis of the study is the time × group interaction effect, which aims to determine the performance differences across groups before and after the intervention, thereby verifying the potential value of music intervention under mental fatigue. Time main effects and group main effects will serve as secondary analysis objectives.

Prior to the main analysis, a one-way ANOVA will be conducted to compare baseline skill performance across the three groups to assess initial group equivalence and ensure the validity of subsequent comparisons. In the main effects analysis, mixed-design repeated measures ANOVA will be used to test the time main effect (whether overall skill performance changes over time), group main effect (whether there are overall differences among the three groups), and the time × group interaction effect (whether skill performance changes differ among the groups). If the assumption of sphericity is violated, the Greenhouse-Geisser or Huynh-Feldt correction will be applied to adjust the degrees of freedom. If the interaction effect is significant, simple effects analysis will be conducted to clarify the performance trends before and after the intervention within each group and to compare differences between groups at each time point.

To control the accumulation of Type I error due to multiple comparisons, all post hoc group comparisons will apply Bonferroni correction. If the study involves multiple primary outcomes or multiple independent hypothesis tests, the Holm-Bonferroni method will be further applied to control the family-wise error rate. In addition, the study will predefine a single primary outcome—ball-shooting accuracy score—while other technical indicators such as shot quality and reaction time will be treated as exploratory outcomes, serving to support and interpret the results but not as primary hypothesis testing targets.

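### The skill analysis never adjusts for the baseline score: a chance baseline gap shifts the change and post-test comparisons in opposite directions, and precision is lost

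*Protocol article*

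**What the plan says.** The Experimental design section of the protocol article sets the order: "The study consists of three main phases (Fig 2): familiarization with the experimental procedure, baseline testing, and the formal experiment". Assignment belongs to the last phase: "During the formal experiment, participants will be randomly assigned to one of the following three groups". Intervention protocols adds that "The baseline test and the formal test will be one week apart", and Data management has paper records entered into the "electronic database within 24 hours and immediately destroyed". Baseline scores can therefore be on file before anyone is allocated.

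On the method of allocation the article says only: "Randomization of group allocation and participant order will be conducted using a random number table generator".

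Statistical analysis makes the time × group interaction of a 2 × 3 mixed ANOVA the core test. If it is significant, simple effects follow, within each group and between groups at each time point. Before this, "a one-way ANOVA will be conducted to compare baseline skill performance across the three groups to assess initial group equivalence"; the stated purpose is to secure the validity of the later comparisons. No consequence is given if the groups differ, and no model contains the baseline score as a covariate.

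**The concern.** The music question is the MF-Mu versus MF-nMu contrast, and the plan offers two readings of it. The interaction compares changes, which fixes the coefficient of baseline at 1. The follow-up compares post-test means, which fixes it at 0. With a pre-post correlation between 0 and 1 and similar variances, the efficient coefficient lies in between. One reading therefore over-corrects a chance baseline difference and the other leaves it uncorrected, so they move in opposite directions.

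The baseline ANOVA does not help. A non-significant result with about 25 per arm does not show balance, and a significant one leads to no stated action. At stake are the precision of the main contrast and the ability to read a trial in which the two fatigue arms happen to start apart.

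**Working it through.** **Inputs.** From Participants: f = 0.25, three groups, two time points, correlation 0.5, "α = 0.05, power = 0.95", 66 required, 76 recruited. Arm size: 76/3 = 25.3, taken as 25. Equal pre and post variances are assumed, and all contrasts are in outcome-SD units.

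**The plan's own figure.** For the within-between interaction, the noncentrality is f² × N × 2/(1 - ρ). At N = 66 this is 0.0625 × 66 × 2/0.5 = 16.5, with 2 and 63 degrees of freedom, and power is 0.9535. N = 63 gives 0.944, so 66 reproduces.

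**Chance baseline gap between two arms.** SD = √(2/25) = 0.283. The 95% range is ±1.96 × 0.283 = ±0.55. P(|gap| > 0.3) = 0.29 and P(|gap| > 0.5) = 0.08. The probability that some pair of the three arms differs by more than 0.5 is 0.18 (simulation).

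**Shift given a realised gap D.**
- Post-test contrast: +ρD = +0.5D.
- Change contrast: ρD - D = -(1 - ρ)D = -0.5D.
- At D = 0.3: +0.15 and -0.15 SD.

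In 200,000 simulated trials of 3 × 25 with no true effect, the slopes on D were +0.500 and -0.500. Both contrasts averaged zero, and the interaction test rejected in 5.1%. The pairwise music contrast also rejected in 5% overall, but in about 8% of trials with |D| > 0.25 and about 16% of those with |D| > 0.5.

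**Standard error of the music contrast, 25 per arm.**
- Post-test only: √(2/25).
- Change: √(2/25) × √(2(1 - ρ)).
- ANCOVA: √(2/25) × √(1 - ρ²).

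| ρ | Post-test | Change | ANCOVA |
|---|---|---|---|
| 0.3 (assumed) | 0.283 | 0.335 | 0.270 |
| 0.5 (protocol) | 0.283 | 0.283 | 0.245 |
| 0.8 (assumed) | 0.283 | 0.179 | 0.170 |

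At ρ = 0.5 the ANCOVA variance is 0.75 times that of either planned reading. The noncentrality at N = 66 becomes 16.5/0.75 = 22, and power rises from 0.954 to 0.989. With ANCOVA, 51 golfers would reach 0.95.

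**Scale.** f = 0.25 means the three mean changes have SD 2 × 0.25 = 0.5. If only MF-nMu declines, by Δ, that SD is Δ√2/3, so Δ = 1.06. A shift of 0.15 is 0.15/1.06 = 14% of it, and about half a standard error (0.15/0.283 = 0.53).

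**The case against.** The case for leaving the plan alone has real force. Randomisation makes both contrasts unbiased, and the interaction test keeps its level. The interaction already uses baseline, only less efficiently. The plan ranks its readings: the interaction is the core hypothesis, and between-group comparisons follow only if it is significant. Those comparisons include the pre-test, so a baseline gap would be visible beside the post-test result. Against the effect the trial is powered for, a shift of 0.15 SD is modest. All of this stands. It limits the point to efficiency and interpretation but does not answer it, because a better estimate is available from data already collected.

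Three stronger readings are tempting, and the article supports none of them.

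- **That allocation is an unrestricted draw that ignores the baseline scores.** The article names the generator and is silent on strata or blocks. Figures 1 and 2 and files S1-S3 are not shown, and a condensed article may leave such detail to them. Simple randomisation would in any case be valid.
- **That the music effect is biased, or that nothing decides between the two readings.** The shifts are conditional on the realised gap, and the hierarchy just described does decide.
- **That matched allocation is the main remedy.** Randomising within ranked triplets from one pool of 75 would cut the SD of the gap to 0.035. Ranking within sessions of an assumed 15 golfers gives only about 0.10, and the step adds little once baseline is in the model.

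**Conclusion.** The point holds as one about the analysis. The Statistical analysis section leaves the baseline score unadjusted in both comparisons and relies on an equivalence test that cannot do what is asked of it. At 25 per arm and ρ = 0.5, the cost is a standard error of 0.283 instead of 0.245 SD for the music contrast. There is also a conditional shift of half the realised baseline gap, of opposite sign in the two readings. The overall type I error is not affected.

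The size depends on similar pre and post variances and on the protocol's assumed correlation. Against the change analysis the gain is larger at a lower correlation (0.335 to 0.270 at 0.3) and small at a high one (0.179 to 0.170 at 0.8). The shift matters more if the true music effect is smaller than the one implied by f = 0.25.

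**What to change.** In Statistical analysis:

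1. Make the primary group comparison an ANCOVA of the post-test accuracy score with the baseline value of the same score as covariate. An equivalent mixed model, with one common baseline mean for all arms, would also serve and fits the planned likelihood handling of missing data.
2. Take the MF-Mu versus MF-nMu contrast from that model, keeping the planned multiplicity correction.
3. Drop the baseline one-way ANOVA as a validity check and report baseline scores descriptively.

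The cost is one degree of freedom and a rewritten paragraph. The sample size need not rise, and the article states that recruitment has not begun.

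Optional: because baseline scores are known before allocation, golfers could be allocated within blocks ranked on the single primary accuracy score. This should be done only if the model includes baseline or block. With the ANOVA as planned, the nominal standard error would be about 15% too large (0.283/0.245 = 1.155), and the 5% test would run at about 2.4%.

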### Intervention protocols

The experiment will be conducted at the university’s golf training facility under the supervision of professional members of the research team, including the university team’s head coach, team doctor, and a national-level golf referee. Data will be collected before and after the intervention, covering questionnaire assessments and golf skill tests. The baseline test and the formal test will be one week apart, and the experiment will take place on the same day of the week and at the same time (9:00–11:00 AM) to ensure sufficient recovery time and minimize the interference of residual effects [55,63,64].

During the mental fatigue induction phase, a 30-minute Stroop task will artificially induce mental fatigue, simulating the mental fatigue state that athletes experience during competitions or training sessions [65]. The Stroop task is a classic cognitive control task widely used for inducing mental fatigue. Research in sports science has shown that a 30-minute Stroop task significantly increases subjective fatigue and reduces sports performance [21,24]. This study will use a smartphone-based version of the Stroop task, where colour words (such as “red” and “blue”) are displayed continuously, but the font colour does not match the word’s meaning. Participants must ignore the word’s meaning and respond only based on the font colour. The Stroop task requires sustained attention, conflict resolution, and cognitive inhibition, leading to cognitive resource depletion and mental fatigue accumulation. During the experiment, all participants will use their smartphones (with brightness and touch sensitivity standardised) and wear earphones to minimise external distractions. Participants in the MF-Mu and MF-nMu groups will undergo mental fatigue induction, while those in the CON group will only read a golf magazine in a relaxed manner.

During the music intervention phase, participants will listen to 15 minutes of classical music to facilitate mental fatigue recovery. Research has shown that short-term listening to classical music can effectively alleviate mental fatigue [60,66–68]. Among classical music, Mozart’s compositions are particularly effective in cognitive function recovery, attention enhancement, emotional regulation, and mental fatigue relief due to their bright and optimistic style, pure and elegant melodies, and harmonious rhythms [69–71]. Therefore, This study selects Mozart’s Eine Kleine Nachtmusik as the intervention music [72], a piece that has been applied in previous mental fatigue recovery studies and has been validated as an effective intervention [66]. The intervention duration is set at 15 minutes, as multiple studies have confirmed this duration to be sufficient to produce recovery effects without causing additional cognitive load or auditory fatigue [66,73,74]. Based on research in the field of music therapy, the intervention volume should be maintained between 50–60 dBA [71,75–77]. The music will be played through a smartphone. Considering that the maximum volume of a smartphone is approximately 105–113 dBA [78], the standardized intervention volume was set at 50% of the maximum (52.5–56.5 dBA), with participants allowed to make slight adjustments to ensure listening comfort. Participants in the MF-Mu group will wear earphones and listen to the music for 15 minutes, while those in the MF-nMu and CON groups will wear earphones in the same environment but without audio, simply sitting at rest for 15 minutes. This experimental design effectively controls for non-musical factors, ensuring that the observed effects can be solely attributed to the music intervention.

The mental fatigue induction and music intervention will be conducted in the same classroom, with the room temperature maintained at 24°C, soft lighting, and no background noise. This study has chosen smartphones instead of computers as the experimental devices because listening to music via smartphones during non-hitting intervals in official golf competitions complies with golf regulations. Thus, using smartphones enhances the real-world applicability of the study’s conclusions in actual competition settings.

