### Visual analog scale

The Visual Analog Scale (VAS) is used to assess participants’ subjective perception of mental fatigue and task motivation levels [79]. The scoring is based on a 100 mm linear scale, where participants mark a point between 0 (none at all) and 100 (extremely intense) to describe their current level of mental fatigue or motivation.

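### The control group reads golf content before golf-skill tests and the Stroop groups do not, so contrasts with CON do not cleanly isolate mental fatigue

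*Protocol article*

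**What the plan says.** Two places in the protocol article describe what the control group does during the 30-minute induction phase.

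- **Experimental design** (text after Fig 2): "Participants not undergoing mental fatigue induction will read some magazine leisurely, a common control in mental fatigue trials". The kind of magazine is not given.
- **Intervention protocols**: "those in the CON group will only read a golf magazine in a relaxed manner". Here the content is golf.

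For the other two groups, Intervention protocols states: "This study will use a smartphone-based version of the Stroop task". The sentence just before the one on group activities applies to everyone: "all participants will use their smartphones (with brightness and touch sensitivity standardised) and wear earphones to minimise external distractions". Whether the magazine is on paper or on screen is not stated.

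In the 15-minute second phase the two non-music groups are matched closely: "those in the MF-nMu and CON groups will wear earphones in the same environment but without audio, simply sitting at rest for 15 minutes".

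On analysis, the Statistical analysis section says: "The core hypothesis of the study is the time × group interaction effect". Simple effects are examined only if that interaction is significant. Motivation is a control variable in Table 2. The VAS "is used to assess participants’ subjective perception of mental fatigue and task motivation levels".

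**The concern.** The participants are competitive university golfers, and they take golf-skill tests directly after the 45-minute intervention period. Golf reading could change their interest, imagery or motivation for those tests. Every CON golfer gets it and no fatigue-group golfer does, so its effect cannot be separated from the effect of being spared the Stroop task.

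CON is the reference for whether fatigue changed performance at all, and one of three groups in the test of the core hypothesis. The Introduction also makes the differing impact of mental fatigue across skills an aim, and that part rests on MF-nMu versus CON. If golf reading helps CON, the apparent harm from fatigue is too large; if it hinders CON, too small.

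The reason given for the reading control is that it is common in mental fatigue trials. That supports leisurely reading in general. The protocol gives no separate reason for golf content ahead of golf outcomes.

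**Working it through.** **1. The groups side by side**

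| Feature | MF-Mu | MF-nMu | CON |
|---|---|---|---|
| First 30 min | Stroop task | Stroop task | Relaxed reading |
| Golf content in those 30 min | None | None | Golf magazine |
| Smartphone and earphones | Yes | Yes | Stated for all participants; reading medium not given |
| Next 15 min | Music | Rest, silent earphones | Rest, silent earphones |

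MF-Mu and MF-nMu differ only in music. MF-nMu and CON differ in cognitive load and in golf content.

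**2. Can the planned measurements separate the two?**
The mental fatigue VAS shows whether the Stroop task raised fatigue. It does not show whether golf reading changed performance. The motivation VAS does not settle the matter either: the Introduction says mental fatigue itself lowers motivation, so a motivation gap between CON and MF-nMu could come from fatigue, from golf reading or from both. Adjusting for motivation measured after the intervention would also remove part of the fatigue effect. The planned ANOVA names no covariate.

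**3. The plan's own figure**
Inputs from Participants: f = 0.25, α = 0.05, three groups (k = 3), two time points (m = 2), correlation 0.5.
λ = f²·N·m/(1 − ρ); df = (k − 1)(m − 1) and (N − k)(m − 1).
- N = 66: λ = 0.0625 × 66 × 2/0.5 = 16.5; df 2 and 63; power 0.9535.
- N = 63: power 0.9436.

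The stated minimum of 66 (22 per group) is reproduced. It does not depend on what CON reads.

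**4. How much a content effect could matter (illustration)**
The documents give no size, so let b be an assumed shift in CON only, in SDs of the change score. At correlation 0.5 the SD of change equals the outcome SD. Assume no true fatigue or music effect, and 22 per group.
- Standard error of a two-group difference in mean change: √(2/22) = 0.30.
- MF-nMu versus CON: two-sided t-test, 42 df, noncentrality b·√(22/2).
- Three-group interaction: group mean changes (0, 0, b), so λ = 22 × (2/3) × b²; F-test with 2 and 63 df. For b = 0.3, λ = 22 × 0.6667 × 0.09 = 1.32.

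| Assumed b (SD) | b in standard errors | MF-nMu vs CON rejects | Interaction rejects |
|---|---|---|---|
| 0 | 0 | 5.0% | 5.0% |
| 0.1 | 0.3 | 6.2% | 6.1% |
| 0.2 | 0.7 | 9.9% | 9.5% |
| 0.3 | 1.0 | 16.3% | 15.6% |
| 0.5 | 1.7 | 36.7% | 36.9% |

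The t-test column is a single unadjusted comparison. The rates are the same for a shift of either sign. They show how sensitive the tests are, not that a shift exists.

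**The case against.** The strongest reply is that the main question is untouched. The aim is the effect of music under mental fatigue, and MF-Mu versus MF-nMu answers it with the same Stroop task in both groups. This stands. It does not remove the point, because CON enters the omnibus interaction that decides whether simple effects are examined, and CON alone carries the fatigue question.

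Second, nothing in the documents shows that leisurely golf reading alters shot accuracy. All groups attend the same golf camp, are told to perform their best, and complete a coach-led 10-minute warm-up before testing; CON also rests for 15 minutes after reading. This stands as well. Any added effect may be small, and its sign is unknown.

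Third, the two descriptions of the magazine can be read as a general statement followed by its detail. That is fair: they are not contradictory, and the Experimental design section does not claim that the reading is neutral. They still differ on a detail that matters, and someone following only the first could run a different control.

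A reader might also infer that CON reads on paper and so lacks the screen exposure of the Stroop groups. The documents do not support that. The preceding sentence puts all participants on smartphones with earphones, and the word only in the CON sentence can simply contrast reading with the Stroop task. The medium is unstated; a device difference is not established.

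**Conclusion.** The point holds for content. As written, contrasts with CON do not cleanly isolate mental fatigue from any effect of golf reading. It limits MF-nMu versus CON and CON's contribution to the time × group interaction, and does not affect MF-Mu versus MF-nMu.

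The size is unknown. The rejection rates above rest on assumed shifts, the planned 22 per group, a correlation of 0.5 and no true effects. A reader might go further and say that the fatigue effect cannot be isolated, or that it is overstated. The documents support neither: the first presumes that a content effect exists, and the second that it favours CON. What is established is an avoidable difference between groups that the planned measurements could not disentangle afterwards. That makes this an inexpensive design improvement rather than a fatal flaw.

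**What to change.** Before recruitment starts (the protocol reports that it had not):

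1. Replace the golf magazine with one fixed, emotionally neutral, non-golf text for the full 30 minutes.
2. Describe it in the same words in Experimental design and in Intervention protocols.
3. State that it is read on the same standardised smartphone with earphones, as Intervention protocols already implies for all participants.

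CON and MF-nMu would then be matched on golf content and on device, in line with the matching already used in the rest phase. The cost is choosing a text and loading it on the phones. A neutral text may be somewhat less engaging than a golf magazine; the mental fatigue VAS, already planned, can check whether it tired CON. Sample size and analysis do not change.

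### The music volume of 52.5–56.5 dBA comes from halving decibel values, so nothing shows that a 50% setting meets the protocol's own 50–60 dBA requirement

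*Protocol article*

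**What the plan says.** All the relevant text is in the protocol article, Methods and design, Intervention protocols.

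- **Target.** Citing music therapy research, the article says that "the intervention volume should be maintained between 50–60 dBA".
- **Device maximum.** The next step opens with "Considering that the maximum volume of a smartphone is approximately 105–113 dBA", citing a source for that figure.
- **Setting.** From this it concludes that "the standardized intervention volume was set at 50% of the maximum (52.5–56.5 dBA"; the closing bracket follows directly.
- **Latitude.** The same sentence continues "with participants allowed to make slight adjustments to ensure listening comfort". No limit on the adjustment is stated.
- **Playback.** "Participants in the MF-Mu group will wear earphones and listen to the music for 15 minutes".
- **Devices.** The paragraph on the Stroop task says that "all participants will use their smartphones (with brightness and touch sensitivity standardised"; sound output is not among the features standardised there. The phone and earphone models used for the music are not stated.

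**The concern.** The setting is presented as following from the device maximum, and both ends of the printed range are exactly half of the two maximum values. A decibel figure is a logarithm of a ratio, so dividing it by two does not correspond to halving the sound.

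The sentence can be read in two ways:

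1. **A 50% volume setting** (the likelier reading). The level then depends on how the phone maps its setting to output, on the earphones and on the recording. The article gives none of these, so the printed dBA range is not supported.
2. **A target level of 52.5–56.5 dBA**, with the percentage merely describing the number. The target is then inside 50–60 dBA, but the percentage does not tell anyone how to reach it.

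On either reading, the halving is the only link shown between the working instruction and the required range. This sentence fixes the dose of the experimental intervention. Staff who apply the 50% rule could miss the protocol's own target, and the published description of the music could then be wrong and not reproducible.

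**Working it through.** **Inputs**, all from Intervention protocols: maximum 105–113 dBA; required level 50–60 dBA; stated level at 50% of maximum 52.5–56.5 dBA.

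**1. Reproducing the printed figure.** 0.5 × 105 = 52.5 and 0.5 × 113 = 56.5. Both ends match exactly.

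**2. What the printed levels mean as a share of the maximum.** The sound pressure ratio for a drop of Δ dB is 10^(−Δ/20).

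- 105 to 52.5 dBA: Δ = 52.5, ratio 10^(−52.5/20) = 0.00237, or 0.24%.
- 113 to 56.5 dBA: Δ = 56.5, ratio 10^(−56.5/20) = 0.00150, or 0.15%.

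**3. What a literal half would be.**

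| Quantity halved | Change | From 105 dBA | From 113 dBA |
|---|---|---|---|
| Sound pressure | 20·log10(0.5) = −6.02 dB | 98.98 | 106.98 |
| Acoustic power | 10·log10(0.5) = −3.01 dB | 101.99 | 109.99 |

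These values follow from the definition of the decibel. They show that halving the number is not halving the output. They do not estimate what a participant would hear at a 50% setting.

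**4. Attenuation needed to meet the target.**

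- From 105 dBA: 105 − 60 = 45 to 105 − 50 = 55 dB.
- From 113 dBA: 113 − 60 = 53 to 113 − 50 = 63 dB.

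One common attenuation serves both ends only at 53–55 dB. This applies if the trial's devices span 105–113 dBA, which the article does not establish.

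**5. Illustration only: a volume control linear in dB.** Assume a total range of R dB, so that the level at 50% is the maximum minus R/2. The values of R are assumptions and come from no document.

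| R (dB) | Level at 50%, maximum 105–113 dBA |
|---|---|
| 40 | 85–93 |
| 60 | 75–83 |
| 80 | 65–73 |
| 100 | 55–63 |

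The printed values appear under this model only if R equals each phone's own maximum (R = 105 and R = 113), that is, if the control runs linearly in dB from 0 dBA. The article states no such assumption. Other volume curves would give other levels.

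**The case against.** The strongest reply is that the printed level has not been shown to be wrong. A control linear in decibels from 0 dBA would give exactly 52.5–56.5 dBA, and other curves might come close. If the range is read as a target, it already lies inside 50–60 dBA, and only the words about 50% are faulty. The protocol speaks of volume, not of sound pressure or power, so the half-pressure and half-power figures measure something it never claimed. The governing 50–60 dBA requirement is in the text, participants may adjust for comfort, and nothing in the article shows that a departure from the range changes the effect of the music. Calibration detail could also sit in the full protocol.

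Part of this stands. The delivered level is unknown, not demonstrably wrong, and the slider values above should not be read as evidence of over-exposure. What does not stand is the derivation. The article prints a specific figure reached by a specific step, and that step does not support it; this is an error in stated text, not a detail left out for brevity. A control that happens to be linear from 0 dBA would make the figure right by coincidence, since the article does not invoke one. Comfort adjustments without a stated limit, made from an unverified starting level, do not secure the 50–60 dBA range.

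**Conclusion.** The concern holds. The range 52.5–56.5 dBA is the result of halving decibel numbers. It establishes neither the level at 50% of maximum volume nor that this level lies within 50–60 dBA. This conclusion rests only on the printed figures and the definition of the decibel.

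The size of any error in the delivered level cannot be determined from the article. It depends on the volume curve, earphones and recording, and it may be nil. The values for particular slider ranges hold only under the assumed linear-in-dB control.

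The consequence is limited to intervention fidelity and to accurate, reproducible reporting of the music dose. Randomisation, sample size, the time × group test and the error rates are untouched. It should be fixed, because it concerns the dose of the intervention under test and the remedy is small.

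**What to change.** Delete the phrase that sets the volume at 50% of the maximum, together with its dBA range. Replace it with wording such as: *For each phone and earphone model used, the volume is set by sound-level measurement of the earphone output with the trial recording so that it lies within 50–60 dBA; participants may make slight adjustments within that range.* This keeps the existing target and only clarifies how it is met.

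The cost is one corrected sentence and a brief measurement per phone/earphone model before the camp. If participants bring their own phones for the music, about 25 people (76/3 ≈ 25.3) could bring many combinations, and measuring earphone output may need an ear coupler. Supplying one common phone/earphone model would reduce this to a single check. Participants lose a little freedom to choose a comfortable level. The design, sample size and analysis do not change. The Status and timeline section reports that neither recruitment nor data collection had begun at the time of writing.
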